### Study population

All elderly persons aged 60 years or older, who were independent in activities of daily living before the injury, presenting to the ED with a unilateral, displaced, extra-articular distal radius fracture (AO/OTA type 23-A2 and A3) [18] and treated with IlluminOss® will be considered eligible for inclusion. The fracture will be classified on lateral (preferably lateral carporadial) and anteroposterior (AP) radiographs.

The inclusion criteria are:Adult men or women with an age of 60 years or olderA unilateral, displaced, extra-articular distal radius fracture (AO/OTA type 23-A2 or A3), as confirmed on X-ray (lateral (preferably lateral carporadial) and AP)Capable of independent activities of daily living prior to index injury*Closed reduction and intramedullary fixation using the IlluminOss® System within 14 days after traumaProvision of informed consent by patient.

* This will be assessed using a simple yes/no question concerning their independence.

The exclusion criteria are:Additional traumatic injuries if this affects treatment, rehabilitation, or function of the affected wristA pathological, recurrent, or open (i.e., Gustilo-Anderson grade II or III) fractureAn impaired wrist function at the affected side) due to arthrosis, rheumatoid disorder, or neurological disorder prior to the injuryA bone disorder (excluding osteoporosis), that may impair bone healing (e.g., osteomalacia, renal osteodystrophy, or Paget’s disease)Patient is unwilling or unable to comply with the after-care protocol and follow-up visit scheduleInsufficient understanding of the Dutch language for adequate comprehension of the treatment information or rehabilitation program, as judged by the attending physician or researcherParticipation in another surgical intervention or drug study.

### Intervention

Following successful closed reduction, patients will undergo fixation with the IlluminOss® System (IlluminOss® Medical, East Providence, RI, USA), using a standardized protocol and the manufacturer’s guidelines (Fig. 1). During the procedure, the fracture is reduced and stabilized. A customized, inflatable, thin walled polyethylene terephthalate (PET; Dacron) balloon is mounted on an insertion catheter. The small diameter compressed balloon (~3.5 mm) is inserted into the medullary canal spanning the fracture site. Next, the delivery sheath is removed, uncovering the balloon. The balloon is then infused with a biocompatible photodynamic liquid monomer via a syringe, causing the balloon to expand. The inflated implant conforms to the shape of the canal and curves from the entry at the radial styloid into the canal. The formed arc within the radial box acts as a support structure to the floor of the articular surface and contributes to a transverse reduction force. The bone is visualized under fluoroscopy to ensure that the fracture has been properly reduced, with the balloon in the appropriate position, fully inflated and contacting the inner diameter of the bone. Upon activation of the light system (Blue Wave 75 VT Photodynamic Light Box), the photo initiator in the monomer rapidly polymerizes and hardens in situ to form a strong hardened nail that provides articular support and canal and rotational stability. This aids fracture healing by primary callous formation and remodeling.

**Fig. 1 Fig1:**
[figure not shown]
Using the IlluminOss® System for fixating a distal radius fracture*. **a** 1.5–2.0 cm incision over the radial styloid process, between the first and second extensor compartment to reach the periosteum. The superficial branches of the radial nerve are protected. **b** Access to the medullary canal and insertion of a 1.5 mm guide-wire. **c** Correct position is verified by intra-operative fluoroscopy. **d** Flexible balloon catheter is placed intramedullary over the guide-wire spanning the fracture. **e** Infusion of liquid monomeric material and expansion of the balloon conforming to the patient’s unique medullary canal. **f** Verification of adequate fracture reduction, correct balloon position, and balloon expansion. **g** Polymerization (hardening) of the infused monomer by applying visible (436 nm) light, creating a patient specific intramedullary implant. * (Photographs and radiographs are used with permission of the patient)

Patients will receive antibiotics prophylaxis according to the local protocol. They are discharged with either a double bandage or a soft cast. No post-operative mobility restrictions will apply, and patients will be allowed to use their wrist as tolerated immediately.

Relevant details of surgery will be collected (e.g., length and diameter of the balloon, time between injury and surgery, duration of the operation) for assessing the effect on outcome. There will be no restriction in the use of (analgetic) medication or other kind of intervention. Details on the use of analgesics will be recorded. Details of physical therapy and rehabilitation will also be recorded. They will not be standardized as evidence favoring a particular approach is not available. Bone growth stimulators (electrical, ultrasound, or magnetic) are prohibited.

All participating surgeons have attended a technique-oriented training course and performed multiple procedures before commencing the study.

### Outcome measures

The primary outcome measure is the Disabilities of the Arm, Shoulder and Hand outcome measure (DASH). This questionnaire is validated and is completed by patients. It reflects the disability experienced by patients with an upper-limb disorder, and is used for monitoring changes in symptoms and function over time [19–22]. The DASH disability/symptom score is the sum of responses to 30 items (scored 1-5), which test a) the degree of difficulty in performing a variety of physical activities (21 items); b) the severity of pain, activity-related pain, tingling, weakness, and stiffness (5 items); and c) the effect on social activities, work, sleep, and self-image (4 items). The total score ranges from zero (no disability) to 100 points (severe disability). At least 27 of the 30 items must be completed. A validated Dutch version is available [23]. The DASH optional modules for Work and high performance Sport/Music (both 4 items, scored 1–5) will also be completed. The score can only be calculated if all items are completed.

The secondary outcome measures are:Patient-Rated Wrist Evaluation (PRWE)Pain level at both sides (VAS)Health-related quality of life: Short Form-36 (SF-36) and EuroQoL-5D (EQ-5D)Time to regaining independence in Activities of Daily Living (ADL)Resumption of work and other activities of daily livingRange of Motion of the wrist at both sidesRadiographic evaluationComplicationsSecondary interventionsHealth care consumption with associated costsProductivity loss with associated costs

The Patient-Rated Wrist Evaluation (PRWE) measures functional outcome in patients diagnosed with a distal radius fracture [24]. In this 15-item questionnaire, patients are asked to rate the level of pain and disability in their wrist from zero (no pain/difficulty) to 10 (worst pain/unable to do) [25, 26]. The PRWE consists of a 5-item Pain subscale, a 6-item Specific Activities subscale, and a 4-item Usual Activities subscale. Responses to the individual subscales are summed. The total score for wrist pain and disability (100 points) is computed by dividing the sum of the ten functional items by two and adding that subtotal (50 points) to the score for the pain subscale (50 points). This provides a score that ranges from 0 (no pain or disability) to 100 (high level of pain or disability). A validated Dutch version is available [27].

Pain level will be assessed using a 100 mm Visual Analog Scale (VAS), ranging from zero (no pain) to 100 (the worst pain possible). Scores for the affected and contralateral side will both be recorded. At each follow-up visit, patients will also be requested to list the type and quantity of analgesics taken.

The Short Form-36 (SF-36) is a validated generic health survey. The 36 items represent eight health domains, which are combined into a Physical Component Summary (PCS) and a Mental Component Summary (MCS) [21, 22, 28–30]. The eight health domains are physical functioning (PF; 10 items), role limitations due to physical health (RP; 4 items), bodily pain (BP; 2 items), general health perceptions (GH; 5 items), vitality, energy, or fatigue (VT; 4 items), social functioning (SF; 2 items), role limitations due to emotional problems (RE; 3 items), and general mental health (MH; 5 items). The score for each domain ranges from 0 to 100 points. They are normalized to and compared with norm scores of the general population of the United States (1998). Herein, each scale has an average of 50 points and a standard deviation of 10 points. A lower SF-36 score indicates poorer quality of life. A validated Dutch version is available [31].

The EuroQol-5D (EQ-5D) questionnaire is validated for measuring health-related quality of life [21, 22, 32, 33]. EQ-5D is recommended as quality of life instrument for trauma patients [34, 35]. It consists of two parts. The EQ-5D descriptive system has five questions (scored 1–3) regarding problems with mobility, self-care, usual activities, pain/discomfort, and anxiety/depression. The resulting scores are converted to a utility score that ranges from zero to one; a lower score reflects a poorer quality of life. The EQ VAS is a self-rated health status measure, consisting of a vertical 100 mm visual analog scale from zero to 100. A validated Dutch version is available [33].

The time to regaining ADL independence will be asked as a single question. The level of work/ADL resumption will be measured using a numeric rating scale.

The range of motion (ROM) of both wrists (i.e., palmar flexion and dorsal extension, ulnar deviation and radial deviation, pronation and supination) will be measured using a goniometer. The loss of ROM will be calculated as ROM _affected side_ - ROM _contralateral side_.

Radiographic evaluation will be done using routinely obtained radiographs. The degree of radial inclination, volar/dorsal tilt and ulnar variance, the amount of comminution, and the radial length will be measured directly in the digital Picture Archiving and Communication System (PACS) of the participating hospital on standard AP, lateral carporadial, or lateral wrist X-rays. Radiographs will be made using a standardized protocol; 1) for the AP radiographs, the shoulder should be held in 90° abduction, the elbow in 90° flexion, and the wrist in neutral position; 2) for the lateral X-rays, the shoulder should be held in a neutral position and the elbow in 90° flexion; 3) for the lateral carporadial radiographs, the lower arm should be positioned on a 20–25° angled wedge.

Radiographic healing and alignment of the distal radius will be evaluated using X-rays. The treating physician and two independent experts will assess the Lidström score for the repeated X-rays of the wrist blinded from the first assessment [36]. X-rays will be blinded and radiographic evaluation will be done by two experts independently. Any discrepancy will be resolved in a consensus meeting.

The following complications will be collected from the patients’ hospital records; 1) skin problems (threatened skin, necrosis); 2) Surgical site infection [37]; 3) radial nerve pathology; 4) vascular injury (hemorrhage, injury to the radial or ulna artery); 5) tendon pathology (abductor pollicis brevis/longus, extensor carpi radialis brevis/longus, extensor pollicis longus); 6) compartment syndrome; 7) secondary dislocation (loss of length, angulation, or rotation); 8) implant failure (balloon breakage); 9) non-union/pseudarthrosis (i.e., no healing or progress towards healing visible at 6 months after surgery); 10) malalignment severe enough to treat surgically; 11) CRPS type I; 12) systemic, generic or other complications.

Secondary intervention within 1 year of surgery will be collected from the patients’ hospital records. Only interventions aimed at relieving pain, treating infection, promoting fracture healing, or improving function will be recorded. They will be categorized as 1) drug treatment (oral or intraveneous antibiotics, other); 2) surgical treatment (incision and drainage, revision osteosynthesis (plate osteosynthesis, intramedullary nail or other), implant removal, other).

A custom-made questionnaire will be designed to collect details of health care consumption and work absenteeism (i.e., production loss). Health care use associated with diagnosis, treatment, and rehabilitation will be collected. This includes medical specialist care, hospitalization, medication, nursing care, physical therapy, and general practice care [21].

The following data will be collected in order to describe the population and intervention:Patient characteristics: age, gender, American Society of Anesthesiologists’ (ASA) classification, tobacco use, comorbidities, medication use, dominant side, sports activities prior to injury, work prior to injury, household composition, and ADL pre-injury.Injury characteristics: mechanism of injury, affected side, AO fracture classification [38], and additional injuries.Intervention characteristics: time between injury and surgery, length and diameter of PET balloon used, duration of surgery, peroperative complications, admission duration at the Intensive Care Unit and in hospital, type and duration of immobilization (including the use of a sling or collar and cuff), time between trauma and the first physical therapy session, and the duration of physical therapy *(*i.e., total number of sessions).

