## Discussion

Despite the frequent occurrence of distal radius fractures, treatment is still at debate. The ultimate goal of treating a distal radius fracture is to restore full wrist function as early as possible. Full range of motion in the wrist declines with disuse and the introduction of early motion following a fracture is critical for the early restoration of normal function, but also for regaining ADL independence. Especially the latter is considered the main strength of the IlluminOss® System. The IO-Wrist study is aimed at determining the effect of operative treatment of distal radius fractures using the IlluminOss® System. Treating patients with this device is expected to result in good and fast functional recovery (i.e., low DASH and high PRWE scores). When comparing outcome with published data on non-operative treatment (i.e., closed reduction and 4–6 weeks plaster cast immobilization, with surgical intervention only if secondary dislocation occurs), we expect similar outcome at 1 year post-injury. However, improved DASH scores are expected to be noticeable until 6 months after treatment initiation, reflecting faster functional recovery in the operative group. Patients operated with IlluminOss® are expected to regain independence sooner and therefore to consume less health care. Improved recovery as well as less total health care use would justify higher costs for the initial surgery. As far as we know, this is the first high-quality study that will evaluate outcome after treating patients with an extra-articular distal radius fracture operated with the IlluminOss® System, using patient-reported, clinical, and economic outcomes.

Four hospitals in the Netherlands participate in this study. The first patient was included on August 31, 2015. Inclusion is expected to be completed within a year. With a follow-up of 1 year data presentation is expected by the end of 2017.

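### The primary DASH score is defined as a plain sum of 30 items, which cannot give the stated 0–100 scale and does not suit forms with 27–29 answers; the PRWE direction and the ROM sign need minor corrections

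*Protocol article*

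**What the plan says.** Three statements in the Protocol article are at issue.

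- **DASH (primary outcome), Outcome measures.** The rule is "The DASH disability/symptom score is the sum of responses to 30 items", each scored 1–5. The same paragraph then says "The total score ranges from zero (no disability) to 100 points (severe disability") and "At least 27 of the 30 items must be completed". No conversion from sum to 0–100 is given. The Sample size calculation works with an important change of 10 points, a reference mean of 23 (SD 19) and a target mean of 13 (SD 10).
- **PRWE (first-listed secondary outcome).** Under Outcome measures, items are rated "from zero (no pain/difficulty) to 10 (worst pain/unable to do"), and the total is described so: "This provides a score that ranges from 0 (no pain or disability) to 100 (high level of pain or disability"). The Discussion, however, describes the expected result as "good and fast functional recovery (i.e., low DASH and high PRWE scores").
- **Range of motion, Outcome measures.** "The loss of ROM will be calculated as ROM" of the affected side minus that of the contralateral side.

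**The concern.** The DASH sentence carries the weight because it defines the primary outcome. A sum of 30 responses, none below 1, cannot reach zero and can exceed 100, so the rule and the range cannot both hold. The important change and the planning means belong to the 0–100 scale, which the written rule does not produce.

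The completeness rule adds a second difficulty. A sum falls whenever an item is left blank, so a patient with three blanks looks less disabled than one with the same answers on a full form. Stating the range alone does not cure this: two conversions that agree on full forms disagree on forms with 27–29 items.

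The other two statements are lighter. The Discussion reverses the direction of the PRWE, and a variable called a loss of motion comes out negative when motion is lost.

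**Working it through.** **Inputs.** From Outcome measures: 30 DASH items scored 1–5, total 0–100, at least 27 items answered; 15 PRWE items scored 0–10, with ten function items halved and five pain items added; ROM loss = affected − contralateral. From Sample size calculation: means 23 and 13, SD 19, change 10, two-sided α 0.05, power 90 %, 38 patients.

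**1. DASH range under the stated rule.**
- 30 items: 30 × 1 = 30 to 30 × 5 = 150.
- 27 items: 27 × 1 = 27 to 27 × 5 = 135.
- Stated range: 0 to 100. Not reproduced.
- The planning means of 13 and 23 lie below 27 and below 30, so neither can be a sum.

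**2. The rescaling that restores the range.** A linear map of the mean item response from 1–5 to 0–100 is (mean − 1) × 25. With all 30 items this equals (sum − 30) / 1.2. Sums of 30, 90 and 150 give 0, 50 and 100.
- Score 23: mean response 1 + 23/25 = 1.92, sum 57.6.
- Score 13: mean response 1 + 13/25 = 1.52, sum 45.6.
- The 10-point change is 57.6 − 45.6 = 12 points of raw sum.

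**3. Forms with missing items.** Take one patient with 27 answers at a mean response of 1.92.
- Sum: 27 × 1.92 = 51.84.
- Unprorated rescaling: (51.84 − 30) / 1.2 = 18.2.
- Mean-based rescaling: (1.92 − 1) × 25 = 23.
- Gap: 23 − 18.2 = 4.8 points.

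In general the gap is (number missing × mean response) / 1.2. At 1.92 that is 1.6, 3.2 and 4.8 points for one, two and three missing items; it grows with the mean response. With 27 items all scored 1, the unprorated version gives (27 − 30) / 1.2 = −2.5, which is outside the scale.

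**4. PRWE direction.** Maximum: 5 × 10 + (10 × 10)/2 = 100, reached when every item is at its worst. The stated range is reproduced, and high is bad. The Discussion says the opposite.

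**5. ROM sign.** Illustrative values, not from the protocol: 50° affected, 70° contralateral. The formula gives 50 − 70 = −20°; the reverse gives +20°. The size is the same and only the sign differs.

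**6. Does the sample size depend on this?** A one-sample normal approximation with SD 19 reproduces the stated number: ((1.960 + 1.282) × 19/10)² = 37.93, rounded up to 38. Change and SD are both on the 0–100 scale. Expressing both as raw sums multiplies each by 1.2 and leaves their ratio, and so the number, unchanged.

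**The case against.** The strongest reply is that the DASH sentence is loose wording about a validated questionnaire. The range and direction follow in the same paragraph, the planning figures can only be on 0–100, and an article may leave scoring detail to the full protocol. On complete forms the sum and the rescaled score are linear transforms of each other, so the Wilcoxon signed rank test and the mixed-model p-values would be the same on either.

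Much of this stands. A reader might infer that the primary outcome will be analysed as a raw sum; the documents do not support that, because the stated range contradicts it. The appeal to condensation does not stand. The article gives a scoring rule for its primary outcome and the rule is wrong, while it sets out the PRWE arithmetic in full. The range also leaves open how forms with 27–29 items are scored.

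A reader might also take 4.8 points as a false improvement in the study result. The documents do not support that either. It is the figure for one patient with the maximum permitted number of blanks at one response level, and no rate of missing items is given. If the same number of items is blank at both visits, much of the bias cancels in the paired difference. The Statistical analysis section offers multiple imputation where necessary, but does not say that it works on items.

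On the PRWE, one might infer that a success criterion is reversed. None exists: the phrase is an expectation in the Discussion, the definition under Outcome measures is complete and consistent, and all tests are two-sided. On ROM, one might infer a contradiction of a stated scale. No scale is stated for it, the formula is explicit, and the mismatch lies between name and sign.

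**Conclusion.** The DASH definition is wrong as written and should be corrected. A sum of 30 items scored 1–5 runs 30–150 (27–135 with 27 items) and cannot give the 0–100 score on which the planning means and the 10-point change rest. Applied to the incomplete forms that the protocol accepts, a rescaled but unprorated sum understates disability. The gap is 4.8 points for a patient with three blanks at a mean response of 1.92, close to half of the important change. That figure assumes that the missing items would have had the same mean as the answered ones, and that the analyst rescales without prorating. The effect on the study mean cannot be determined from the documents.

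The PRWE wording is a real reversal but drives no test. The ROM point is a naming and sign matter with the magnitude intact; it would matter only if a reported value or regression coefficient for *loss* were read with the wrong sign. Both are minor. None of the three changes the sample size or the planned tests.

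**What to change.** - **DASH.** Replace the summation sentence with: the score is (mean of answered items − 1) × 25, calculated if at least 27 of the 30 items are answered. This gives 0–100 for every accepted form and one rule for 27 to 30 answers.
- **PRWE (minor).** In the Discussion, describe good recovery as low DASH and low PRWE scores.
- **ROM (minor).** Either call affected minus contralateral the difference in ROM, or keep the name and compute contralateral minus affected, so that a positive loss means lost motion.

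The cost is three sentences, with no change to data collection, sample size or tests. The DASH rule should be settled before scoring is programmed.

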### Sample size calculation

For case series, a generally accepted assumption is that introducing and implementing a (relatively new) surgical technique requires 30 patients [39]. A formal sample size calculation for this study is based on the DASH score (primary outcome measure). The minimal important change for the DASH score is 10 points [19]. Based on literature data we expect a mean DASH of 23 (SD 19) in non-operatively treated patients [40, 41]. In order to detect a 10-point improvement (mean 13, SD 10) in patients treated with IlluminOss® with a two-sided α of 0.05 and a 90 % power (β = 0.10), at least 38 patients are needed. Anticipating 10–15 % loss to FU and 10 % mortality, 50 patients will be enrolled.

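### The derived loss of wrist motion takes the opposite wrist as the pre-injury reference, but the entry criteria do not screen that wrist for prior impairment, so the loss can be understated in some eligible patients.

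*Protocol article*

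**What the plan says.** All places are in the protocol article.

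- **Outcome measures, definition.** "The range of motion (ROM) of both wrists" is measured with a goniometer, and "The loss of ROM will be calculated as ROM" of the affected side minus that of the contralateral side. Motion of the wrist on both sides is itself a listed secondary outcome; the difference is derived from it.
- **Study procedures, Table 1.** Range of motion is first measured at the 2-week visit and then at every later visit. There is no pre-injury measurement.
- **Study population, exclusion criteria.** Prior impairment of wrist function from arthrosis, rheumatoid disease or neurological disease excludes a patient only if it is on the injured side. Additional injuries exclude a patient only if they bear on the treatment, rehabilitation or function of the injured wrist.
- **Study population, inclusion criteria.** The index fracture must be unilateral, and patients are at least 60 years old.
- **Outcome measures, baseline data.** The list of patient characteristics includes "comorbidities, medication use, dominant side, sports activities prior to injury", and additional injuries appear among the injury characteristics. A history of the opposite wrist is not named.

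**The concern.** The difference between sides can be called a loss only if the opposite wrist shows what the injured wrist could do before the fracture. No other reference is available, because measurement starts after surgery. The protocol recognises that arthrosis, rheumatoid disease and neurological disease can impair a wrist, since it excludes patients for them, but it applies that screen to only one of the two wrists in the formula. In a population aged 60 or older, a patient with an arthritic opposite wrist, or an old fracture there that healed with lasting stiffness, can enter the study, and that wrist becomes the reference.

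At stake is the credibility of the derived loss figure. The study is a case series without a control group, so no second arm exists in which such an error would cancel.

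**Working it through.** **1. Plan's own figures.** The plan states no figure for range of motion. Its only computed figures are for DASH, and they reproduce with a one-sample formula:

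- For "with a two-sided α of 0.05 and a 90 % power (β = 0.10), at least 38 patients are needed": n = SD² × (z₀.₉₇₅ + z₀.₉₀)² / difference² = 19² × 10.507 / 10² = 37.93, so 38.
- For "Anticipating 10–15 % loss to FU and 10 % mortality, 50 patients will be enrolled": 38 / (0.90 × 0.85) = 49.67, so 50.

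Neither depends on range of motion, and nothing below changes them.

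**2. What the formula returns.** Let A₀ be the pre-injury motion of the injured wrist, A its motion at follow-up, and C the motion of the opposite wrist. Let c = A₀ − C be the shortfall of the opposite wrist.

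- True change = A − A₀.
- Formula = A − C = (A − A₀) + c.

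As written, lost motion appears as a negative number. A positive c moves the result towards zero or beyond it, degree for degree.

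**3. Illustration for one patient.** Assumed values, not in the documents: A₀ = 70, A = 55, so the true change is −15 degrees.

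| Shortfall c | C = 70 − c | Formula 55 − C |
|---|---|---|
| 0 | 70 | −15 |
| 10 | 60 | −5 |
| 15 | 55 | 0 |
| 20 | 50 | +5 |

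**4. Which eligible patients have a non-zero c.**

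| Situation | Removed by the criteria? | Effect on apparent loss |
|---|---|---|
| Simultaneous fracture of the opposite distal radius | Yes, fracture must be unilateral | none |
| Arthrosis, rheumatoid or neurological impairment of the opposite wrist only | No | too small |
| Old opposite fracture with lasting stiffness | No | too small |
| Old opposite fracture, fully recovered | No | none |
| Equal stiffness on both sides, cause not listed | No | none |
| Injured wrist already stiff from an unlisted cause | No | too large |

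**5. Cohort mean.** If a share p of patients has shortfall c and the rest have none, the mean loss is understated by p × c. Both p and c are assumptions:

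- 0.05 × 15 = 0.75 degrees
- 0.10 × 10 = 1.0 degree
- 0.20 × 30 = 6 degrees

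With 50 patients, a single patient with a 30 degree shortfall moves the mean by 30 / 50 = 0.6 degrees.

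**The case against.** The opposite limb is a defensible internal reference when pre-injury motion cannot be measured. Motion of each wrist is already a listed outcome at all five visits, so a reader who distrusts the difference has both components. The study is descriptive, the comparisons with published non-operative results that it sets out concern DASH and recovery, and no test or decision turns on the loss of motion. All of this stands, and it limits the weight of the point.

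Three stronger readings are tempting, and the documents do not support them:

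- **That every patient with a previously affected opposite wrist will show too small a loss.** A recovered fracture or equal stiffness on both sides gives c = 0.
- **That the error always favours the device.** The affected-side exclusion covers three named causes only. An injured wrist that was already stiff for another reason stays eligible and makes the loss look larger. The net direction depends on frequencies that the documents do not give.
- **That these patients cannot be identified afterwards.** Motion and pain of the opposite wrist are recorded at each visit, and comorbidities and additional injuries at baseline. The article may also condense a more detailed case report form, so the missing history item is not in itself a finding.

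Identification from these data is still only partial. A low opposite-side reading cannot separate a one-sided deficit from equal stiffness on both sides, and a stiff wrist need not hurt. Nor does the objection reach the core: the formula and the criteria are both stated in full, and the criteria do not secure what the formula assumes.

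**Conclusion.** The point holds as a limited defect in a derived secondary outcome. In an eligible patient whose opposite wrist had less motion than the injured wrist had before the fracture, the stated formula understates the loss by the full deficit. This follows from the definition and needs no assumption.

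The effect on the cohort mean is unknown. The range of 0.75 to 6 degrees rests wholly on assumed shares (5% and 20%) and assumed deficits (15 and 30 degrees), and it takes no account of errors in the other direction. The upper end would need one patient in five to have a large one-sided deficit, for which the documents offer no basis. The primary outcome, the sample size and the raw motion of each wrist are unaffected. The change is worth making because it is cheap, not because the study's main conclusion is at risk.

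**What to change.** 1. Record at baseline, as a yes/no item, whether the opposite wrist has prior impairment, a previous fracture or a current injury. For patients already enrolled, take this from the hospital files, which are checked at scheduled visits anyway.
2. Add one sentence to the outcome definition: the side-to-side loss is calculated only in patients with an unimpaired opposite wrist or, at the least, is reported with and without the others.
3. Report absolute motion of the injured wrist for all patients. It is already measured.

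Nobody needs to be excluded from the study. The cost is one form item and one sentence; the downside is that a few patients drop out of the side-to-side figure.
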